### 2.3. Sampling and Recruitment

We conducted formative research (Figure S2) to prepare for the implementation of our intervention. We previously described how we estimated the sample size using the Lynch formula [27]. The target population was all the public school children in Metro Manila, where in School Year 2014–2015 a total of 2,059,447 public school children (1,373,852 elementary and 685,595 secondary school children) were enrolled [23]. We inflated the sample by 30% and 45% to account for nonresponse and refusal, respectively, and then inflated the sample by another 5% to account for differences in schools’ enrollment sizes. The target sample size was N = 760; we enrolled 756 students at baseline and 703 students at the 8-month follow-up (retention rate: 86%) (Figure 3).

We selected schools located in Manila, Navotas, and Quezon City (Figure 4) because they were geographically and demographically representative of cities in Metro Manila. We recruited the school principals from the 15 public schools that participated in our previous observational study [27]. We used convenience, rather than probabilistic, sampling, choosing to revisit the same 15 schools because of existing relationships of trust and cooperation with school principals and personnel. These factors can facilitate communication and collaboration, which were crucial because we aimed to maintain a long-term working relationship with schools in spite of our limited resources in time, personnel, and materials. We previously described our multi-stage cluster sampling strategy [27]. Based on the school’s enrollment size, 1–2 class sections were selected to obtain a target sample of ~50 students per school. We recruited entire class sections as a whole rather than groups of students from multiple class sections so as not to interrupt on-going classroom instruction with our research activities. We decided not to re-recruit the students from our previous observational study as a new school year had begun, resulting in students advancing up to the next grade level (e.g., from grade 5 to 6) and moving to different class sections, as well as some students transferring to different schools that were not involved in our study. No monetary reimbursement was offered to school principals, and all schools were compensated (Table S6) with printed research portfolios, certificates of appreciation, classroom viewings of an educational film promoting handwashing, and hand hygiene gel.

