After obtaining data from the children, research assistants completed the school restroom inspection checklist, took photos of WaSH facilities, and interviewed school principals or representatives, inputting all data into the app. We obtained school administrative data, e.g., budget for maintenance and other operating expenses, from the DepEd. At the end of each workday, research assistants discussed their work with each other, shared lessons learned, and identified areas for improvement. Upon accessing an internet hotspot, we used the app to transmit anonymized data to a central database via cloud storage. Research assistants periodically checked uploaded data to verify the completeness of data upload and identify discrepant, missing, or duplicate data. When needed, appropriate remedial action was taken, e.g., re-training research assistants or clarifying instructions for children.

After completing baseline surveys, we assigned two schools to the control arm and 13 schools to the intervention arm (Figure 3). We purposefully assigned two schools to the control arm because one school had a school principal who directly asked us to participate in our previous observational study. The other school was integrated (offering all possible grade levels, from kindergarten to grade 12) and was the location where we had pilot-tested our survey instruments before the observational study. We randomly allocated schools in the intervention arm to one of four groups. One research assistant and the research supervisor conducted randomization in Microsoft^©^ Excel as follows: (1) In one column, we listed the names of the 13 schools in the intervention arm, with one row representing one school. (2) In another column, we listed the four intervention groups (A, B, C, and D), with one row representing one group. We previously determined how many schools would be allocated to each group (Table S1). (3) In a third column, we used Excel’s random number function and ranked the schools, assigning each school to either group A, B, C, or D (Table S1). Except for the research supervisor, all research assistants, study participants (children), school personnel, and parents were blinded to the assignment of schools to the intervention arm and subsequent random allocation to intervention groups A–D.

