#### 2.8.2. Inferential Statistical Analyses

To address study aims 1 and 3 (Figure 2), we will compare the study arms, using two-sided tests for primary outcomes. For continuous variables, we will use the *t*-test to calculate the mean weight differences between the control and intervention arms. For binary variables, we will use Poisson regression to compare the control and intervention arms according to their relative risk (RR). We will use multiple logistic regression models to analyze exposure-response: g = (E[Ai]) = β0 + β1Bi + γCi, where Ai is the primary outcome of interest, g( )  is the appropriate link function (identity for height and weight, logistic for stunting and poor health literacy), Bi is the continuous exposure of interest, and Ci is the vector of confounders. We describe proposed models in Box S2 and will describe full models in a forthcoming paper [25].

To assess risk factors of health, health literacy, and handwashing outcomes, we will use multiple logistic regression models that account for school-level clustering, estimate precision with 95% confidence intervals (CI), and *p*-values, and produce adjusted odds ratios (aORs). Clustering by school takes into account potential intragroup correlation among children from the same school and enables us to adjust the SE of estimates. aORs control for possible confounders (e.g., children’s age and sex, parent’s educational background and employment status, presence of toilet and handwashing basin inside home, household food insecurity). We will use confounders to calculate an adjusted effect estimate to account for baseline differences between the control and intervention arms. We will use three multiple logistic regression models (Box S2): (1) model A for poor hygiene literacy only, poor handwashing literacy only, and both poor hygiene literacy and poor handwashing literacy; (2) model B for malnutrition, i.e., stunting only, undernutrition only, and overnutrition only; and (3) model C for poor health status only, extreme hunger only, and both poor health status and extreme hunger.

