We will use generalized linear mixed models (GLMMs), which are appropriate for longitudinal data, to determine if the intervention was effective in improving our outcomes of interest. GLMMs are useful for measuring intervention impacts in complex datasets, i.e., when different types of variables (e.g., binary, continuous) are assessed at different time periods, particularly when assessments are made at the group- rather than individual-level. We will use GLMMs to estimate the effect of each intervention compared to the control group. To measure the intervention’s impact, we will estimate differences between pre- and post-intervention outcomes.

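### With only two control schools, the usual school-clustered standard error cannot support the adjusted arm effect: a nominal 5% test would reject a true null about 21–27% of the time

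*Protocol article*

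**What the plan says.** Section 2.5.3 describes the assignment: "we assigned two schools to the control arm and 13 schools to the intervention arm". It was not random: "We purposefully assigned two schools to the control arm". Section 2.3 gives the cluster size ("1–2 class sections were selected to obtain a target sample of ~50 students per school") and the totals: "The target sample size was N = 760; we enrolled 756 students at baseline and 703 students at the 8-month follow-up".

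Section 2.8.2 then plans multiple logistic models that allow for clustering by school, with 95% confidence intervals, p-values and adjusted odds ratios: "Clustering by school takes into account potential intragroup correlation among children from the same school and enables us to adjust the SE of estimates". The paragraph opens with risk factors, but it also states: "We will use confounders to calculate an adjusted effect estimate to account for baseline differences between the control and intervention arms". The next paragraph brings in a second family of models: "We will use GLMMs to estimate the effect of each intervention compared to the control group".

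Section 2.8 says that each intervention group will be compared with control, so all four comparisons rest on the same two schools. The software is Stata 15. The article does not mention the small number of clusters or any correction for it.

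**The concern.** This point is about the analyses that do allow for clustering. A cluster-robust standard error estimates each arm's variance from the spread of school totals within that arm. With two control schools of similar size, the two residual totals must offset each other. The control arm's variance, which is the larger part of the variance of the arm effect, then rests on one degree of freedom and is biased downward. A normal reference, or a t reference with 14 degrees of freedom, treats it as far better known than it is.

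At stake is how the results will be read. Clustered odds ratios look as if the school design has been dealt with, so readers will trust them over crude tests. If their intervals for the arm effect are much too narrow, ordinary differences between two schools and the other thirteen can be reported as intervention effects on stunting, literacy or health status. The multiplicity adjustment in Section 2.8 cannot repair this, because it needs valid p-values to start from.

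**Working it through.** **Inputs.** From the article: 2 control and 13 intervention schools, about 50 children per school (756/15 = 50.4 at baseline, 703/15 = 46.9 at follow-up), two-sided tests, and 5% implied by the 95% intervals. Assumed because the article does not give them: the intracluster correlation (ICC, varied from 0 to 0.2), outcome prevalence (10%, 25% and 50%; Section 1.1 cites 24.5% stunting), the variance estimator (cluster sandwich with factor G/(G−1), G = 15), and package sizes 3, 3, 3 and 4 (Table S1 is not shown).

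**1. The plan's own design figure.** The article states no error rate for the clustered test; its only design figure is the target of 760. The Lynch formula with N = 2,059,447 and assumed p = 0.5, d = 0.05, Z = 1.96 gives 384.1. With the three stated inflations, 384.1 × 1.30 × 1.45 × 1.05 = 760.2. The figure is reproduced. It is a count of children and says nothing about how many schools an arm comparison needs.

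**2. Size of the downward bias.** Take equal school sizes and between-school variance σ² of school means.
- True variance of the arm difference: σ²(1/2 + 1/13) = 0.577σ².
- Expected sandwich variance: (15/14)σ²[(2−1)/2² + (13−1)/13²] = (15/14)σ²(0.250 + 0.071) = 0.344σ².
- Ratio: 0.344/0.577 = 0.60, so on average the variance is understated by about 40%. Of the sum 0.321, the control arm supplies 0.250 (78%), on one degree of freedom.

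**3. Rejection of a true null, 2 versus 13 schools** (simulated, 40,000 trials per setting, beta-binomial and logit-normal school effects):

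| Test of the arm effect | Rejection at nominal 5% |
|---|---|
| Clustered logistic, z | 24.7–26.9% |
| Clustered logistic, t(14) | 21.4–23.8% |
| Clustered logistic with five covariates, z | 24.5–25.9% |
| Clustered logistic with five covariates, t(14) | 21.2–22.5% |
| School-level t-test, 13 df, same data | 4.4–6.1% |

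The clustered rate is about 25% (z) even at ICC = 0. With 7 versus 8 schools, the same clustered z-test gives 8.1%. The two-school control arm is therefore the main cause.

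**4. Each package versus control, one five-group model.** With z, 21.4–23.4% (23.6% with age and sex adjustment and unequal school sizes). With t(14), 18.6–20.2%. The range is roughly 18–24%.

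**5. Mixed model with a school random intercept and Wald z.** In a balanced normal approximation:
- two arms, REML: P(|t₁₃| > 1.96) = 7.2%; ML: P(|t₁₃| > 1.96√(13/15)) = 9.1%;
- five groups, REML: P(|t₁₀| > 1.96) = 7.8%; ML: P(|t₁₀| > 1.96√(10/15)) = 14.1%.

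A simulated linear mixed model fitted by ML gave 9.1%, 11.5% and 13.9% per package at ICC 0.01, 0.02 and 0.05. Binary mixed models and pre/post differences were not simulated.

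**6. The alternative.** School-level log-odds t-tests gave 5.8% and 3.9% (13 df) and 5.5% and 4.6% per package (10 df) at ICC 0.02 and 0.05, with 1,500 trials each. These are unadjusted; the confounder-adjusted two-stage version was not simulated.

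**The case against.** The strongest reply is that the plan may not use these models for the arm effect at all. The paragraph is introduced as a risk-factor analysis, and the next paragraph gives the judgement of effectiveness to the mixed models. The sentence on an adjusted control-versus-intervention estimate names no model, and Box S2, which describes the proposed models, is not shown. The article also names neither a sandwich estimator nor a reference distribution, and an article may leave such detail to a fuller plan. All of this stands, and it makes the 21–27% conditional. It does not remove the point: the adjusted arm estimate is promised inside the clustered-logistic paragraph, and the usual Stata form of that analysis fails with two control schools.

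Three stronger readings are tempting and not supported.
- A reader might infer that the statement about adjusting the standard error is false throughout. The calculations show failure only for the arm coefficient.
- A reader might carry the 21–27% over to the mixed models. Their figures are lower, and they too assume a Wald z-test that the article does not specify.
- A reader might quote the simulated chance of about 50% that at least one of four packages looks effective for a given outcome. That counts four unadjusted tests and assumes the group sizes, whereas Section 2.8 commits to an adjustment for multiple arms. It is not the error rate of the planned procedure.

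It is also fair to say that no test makes this a randomised comparison with control. The Discussion concedes the bias from non-random assignment. The error rates above assume exchangeable schools, and selection bias comes on top.

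**Conclusion.** The concern holds in conditional form. If the arm effect is taken from the school-clustered logistic models with an uncorrected cluster-robust standard error, a nominal 5% test has a true size of about 21–27% for 2 versus 13 schools and about 18–24% for each package versus control. The two-arm result depends little on ICC, prevalence or covariates. It depends on the two control schools and on the assumed estimator; the package result also rests on assumed group sizes. The mixed models, if tested with a Wald z and a school random intercept, run at about 7–14% per comparison (REML at the low end, ML at the high end). The plan should be changed before arm comparisons are reported. The clustered models remain usable for child-level risk factors.

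**What to change.** State in Section 2.8.2 that no arm effects or arm p-values will be read from the clustered logistic models, and keep those models for child-level risk factors.

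For arm comparisons, use a two-stage school-level analysis. Regress each child outcome on the confounders without arm, form one summary per school, and compare arms using the pooled between-school variance with a t reference: 13 degrees of freedom (15 − 2) for two arms and 10 (15 − 5) for the five-group model. For continuous outcomes, a REML mixed model with a school random effect and Kenward-Roger degrees of freedom is an alternative.

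The cost is a wording change and some extra analysis, with no new data. Intervals for the arm effects will be wider. The pooled variance assumes equal between-school variance in the arms, which two control schools cannot check. The change corrects the error rate only if schools are exchangeable. It does not remove the bias from choosing the control schools purposively, so comparisons with control should still be reported as non-randomised.

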#### 2.5.2. Assessing Secondary Intervention Outcomes

First we assessed children’s overall health status, extreme hunger prevalence, and satisfaction with and perceived cleanliness of schools’ WaSH facilities, measured by binary variables, via questionnaire (Table S6). We assessed acute dehydration, measured by incidence of highly concentrated urine (U_sg_ ≥ 1.020) [33,37,38] (Table 1), via urinalysis using urine test strips (Insight Urinalysis Reagent Strips, Acon Laboratories Inc., San Diego, CA, USA). Urine test strips are an affordable, easy to use, and reliable way to perform urinalysis in field settings [39]. Second we assessed school principals’ satisfaction with schools’ WaSH facilities and children’s hygiene practices, measured by binary variables, via interview. Third we assessed, via observation, schools’ WaSH adequacy, measured by continuous and binary variables describing availability, accessibility, cleanliness, and functionality, according to guidelines from the Philippines DepED and Department of Health (DOH) [35,40]. We previously reported the data collection tools we used for conducting health examinations, interviews with school principals, and school restroom inspections [27]. Data collection tools were pilot-tested and improved prior to beginning this trial.

During our previous observational study, we found that children were avoiding or not using school restrooms, possibly due to a perceived lack of cleanliness or lack of privacy. Findings indicated that avoidance and non-use of school restrooms increased children’s risk of diarrhea. Thus, we aimed to see if our intervention was effective in improving children’s perceptions about school restrooms, with the hope that children would use school restrooms rather than avoid using them. Also, we found that school WaSH policies were in place, yet school principals reported being unsatisfied with WaSH facilities and children’s hygiene behaviors. School principals’ perceptions about WaSH could affect efforts to implement, maintain, and sustain improvements, all of which influence children’s health and hygiene behaviors. Thus, we aimed to see if our intervention was effective in improving school principals’ perceptions about school WaSH facilities.

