#### 2.8.1. Descriptive Analyses

We will conduct descriptive analyses, pre- and post-intervention, to measure study participation, demographic characteristics, and outcomes of interest. We will report baseline characteristics for all five study arms. For each primary and secondary outcome, we will report results (e.g., means, proportions) for each arm, including the estimated effect size and precision. To describe exposure to inadequate WaSH at school and at home, we will measure frequencies and interquartile ranges (IQRs) relevant to schools’ and homes’ WaSH facilities. Data from school inspections will be summarized at the school-level by measuring the mean scores of individual facility inspections. To describe outcomes of poor health literacy, poor handwashing, and malnutrition, we will measure prevalence rates using contingency tables with estimates of standard error (SE) and precision.

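### Models A and C use 'only' and 'both' outcomes, so the adjusted odds ratio for one condition depends on the other; model each condition as 'any' instead

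*Protocol article*

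**What the plan says.** Section 2.8.2 of the protocol article announces: "We will use three multiple logistic regression models (Box S2". Two of the three split their outcomes by overlap:

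- Model A: "model A for poor hygiene literacy only, poor handwashing literacy only, and both poor hygiene literacy and poor handwashing literacy".
- Model C: "model C for poor health status only, extreme hunger only, and both poor health status and extreme hunger".
- Model B also uses the word 'only' but has no combined category: "model B for malnutrition, i.e., stunting only, undernutrition only, and overnutrition only".

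The same paragraph gives the purpose of this modelling ("To assess risk factors of health, health literacy, and handwashing outcomes, we will use multiple logistic regression models"). Before listing the three models it adds: "We will use confounders to calculate an adjusted effect estimate to account for baseline differences between the control and intervention arms".

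Elsewhere the conditions carry no 'only' restriction:

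- Section 2.5.2 lists overall health status and hunger among separate binary secondary outcomes ("extreme hunger prevalence, and satisfaction with and perceived cleanliness of" the facilities).
- Section 2.8.1 says "To describe outcomes of poor health literacy, poor handwashing, and malnutrition, we will measure prevalence rates".
- The exposure-response formula in section 2.8.2 names poor health literacy as an outcome without qualification.
- Section 2.5.1 defines the two literacy outcomes as continuous scores.

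**The concern.** Once 'both' is an outcome of its own, 'only' in models A and C most naturally means 'without the other condition'. A child with poor hygiene literacy and poor handwashing literacy is then not a case of 'poor hygiene literacy only', although that child has poor hygiene literacy. The same applies to poor health status and extreme hunger.

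The 'only' odds ratio therefore mixes two things: the factor's relation to the condition named, and its relation to the condition that moves children between 'only' and 'both'. Suppose a factor goes with better handwashing literacy and has no relation to hygiene literacy. It shifts children from 'both' to 'poor hygiene literacy only', and so looks like a risk factor for poor hygiene literacy. A reader would take the reported odds ratio as a statement about hygiene literacy, which it is not.

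**Working it through.** The documents give no prevalence, overlap or odds ratio for these outcomes, so there is no published figure to reproduce. All prevalences and associations below are assumptions, shown over a range.

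**Set-up.** Let *a* be the prevalence of condition 1, the same in both comparison groups (true odds ratio 1.00). Let *b* be the prevalence of condition 2, which falls from *b*0 to *b*1. Let ψ be the odds ratio between the two conditions within each group. The proportion with both, *x*, solves

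x(1 − a − b + x) = ψ(a − x)(b − x).

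Then 'condition 1 only' is o = a − x, and 'neither' is n = 1 − a − b + x. The subscript 0 marks the group without the factor and 1 the group with it.

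- Children with both scored as non-cases: OR = [o1/(1 − o1)] / [o0/(1 − o0)].
- Children with both left out: OR = (o1/n1) / (o0/n0).

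**Worked case:** a = 0.50, b from 0.50 to 0.30, ψ = 3.

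- Without the factor: x = 0.317, o = 0.183, n = 0.317.
- With the factor: x = 0.206, o = 0.294, n = 0.406.
- Non-cases: (0.294/0.706) / (0.183/0.817) = 1.86.
- Left out: (0.294/0.406) / (0.183/0.317) = 1.26.
- Condition 1 coded as 'any': 0.50 in both groups, OR 1.00.

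**Range** (condition 1 unchanged throughout):

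| a | b0 to b1 | ψ | OR, both = non-case | OR, both left out |
|---|---|---|---|---|
| 0.50 | 0.50 to 0.30 | 1 | 1.62 | 1.00 |
| 0.50 | 0.50 to 0.30 | 3 | 1.86 | 1.26 |
| 0.50 | 0.50 to 0.30 | 6 | 2.12 | 1.49 |
| 0.40 | 0.40 to 0.25 | 1 | 1.36 | 1.00 |
| 0.40 | 0.40 to 0.25 | 3 | 1.55 | 1.19 |
| 0.40 | 0.40 to 0.25 | 6 | 1.73 | 1.36 |
| 0.30 | 0.30 to 0.20 | 1 | 1.19 | 1.00 |
| 0.30 | 0.30 to 0.20 | 3 | 1.32 | 1.13 |
| 0.30 | 0.30 to 0.20 | 6 | 1.44 | 1.25 |

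A second grid gives similar results: condition 1 at 20% or 40%, condition 2 halved from 30% or from 50%, ψ = 1, 2 or 4. The odds ratio is 1.26–2.28 with non-case scoring. With children who have both left out, it is 1.00 under independence and 1.11–1.47 for ψ = 2–4.

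**No exact null is needed.** If condition 1 improves from 40% to 36% and condition 2 from 50% to 25%, the 'any' odds ratio for condition 1 is (0.36/0.64) / (0.40/0.60) = 0.84. The 'only' odds ratio with non-case scoring is 1.48–1.92 for ψ = 1–4. With children who have both left out, it is 0.84–1.21.

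**The case against.** Several points stand against a stronger claim.

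- **The coding is not stated.** The article does not say whether a child with both conditions is a non-case or is left out. It refers to Box S2, which is not at hand. Leaving such children out shrinks the artefact and removes it under independence. Some association is likely between two literacy scores from one questionnaire, so it would probably not vanish.
- **'Only' could mean 'modelled singly'.** In model B it may well mean that: undernutrition and overnutrition cannot coexist under the Table 1 cut-offs, and no combined category is listed. If the same sense were meant in A and C, there would be no artefact. The separate 'both' outcome makes this the less natural reading, but the text does not rule it out.
- **The mismatch is not equally direct for both models.** For model C it is with section 2.5.2. For model A it rests on section 2.8.1 and the exposure-response formula, which speak of poor health literacy as a whole. Section 2.5.1 has continuous scores, so no section defines 'any poor hygiene literacy' as an outcome.
- **The 'both' outcome is also modelled.** With condition 1 unchanged it falls (odds ratio 0.44–0.60 in the second grid), so a careful reader could see the shift. That does not make the 'only' odds ratio interpretable by itself.

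A reader might infer that the trial's efficacy analysis will report benefit as harm. The document does not support that. Models A to C are introduced for risk factors. Arm effects are assigned to t-tests and Poisson regression for primary outcomes, and to generalized linear mixed models, none described with 'only' coding. The sentence on an adjusted arm estimate shares the paragraph but does not name these models as its source.

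**Conclusion.** The point holds in a limited form. As most naturally read, models A and C estimate odds ratios for mutually exclusive categories, and these do not measure the association with the single condition. The false odds ratio, for a factor that improves only the other condition, is about 1.2–2.1 if children with both are non-cases. If they are left out, it is 1.0 under independence and about 1.1–1.5 under positive association. These sizes rest on assumed prevalences of 30–50% and between-condition odds ratios of 1–6.

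The effect falls mainly on the risk-factor odds ratios. It reaches the arm comparison only if the adjusted effect estimate comes from models A and C, or if the mixed models reuse the 'only' coding; the article establishes neither. This should be fixed before results are reported, but it does not by itself undermine the designated intervention analyses.

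**What to change.** In section 2.8.2 and Box S2, make the outcomes of models A and C any poor hygiene literacy, any poor handwashing literacy, any poor health status and any extreme hunger, with one model for each. This coding returns an odds ratio of 1.00 in every scenario above in which the condition is unchanged.

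If the overlap is of interest, keep the only/both split as a descriptive table or a multinomial supplement and state its reference category. A multinomial contrast with 'neither' is the left-out case above, so it keeps the smaller artefact. Its 'only' contrasts should not be read as effects on the single condition.

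State also that any adjusted arm estimate and the mixed models use the 'any' outcomes or the scores.

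The cost is recoding existing variables and rewording section 2.8.2 and Box S2. No new data are needed.
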